## Abstract

**Introduction:**

Currently, there are many diagnostic strategies for in-stent restenosis (ISR) used clinically, including invasive coronary angiography (ICA), coronary computed tomography angiography (CCTA), and Fractional Flow Reserve (FFR). CCTA is not recommended for post-stent implantation patients owing to suboptimal image quality caused by artifacts. The FFR application is limited by its procedural complexity. Precise evaluation may be achieved by using computed tomography-derived fractional flow reserve (CT-FFR), which combines computational fluid dynamics (CFD) with CCTA. Anatomical and functional assessments of ISR lesions could be integrated effectively as well in this way. However, the computational complexity and prolonged processing time may hinder its utility in clinical use.

**Methods:**

This study is a multicenter, prospective, diagnostic study, aiming to establish a deep learning-based CT-FFR model for the accurate assessment of ISR and to validate its diagnostic performance using invasive FFR as the reference standard. This study will be carried out in Beijing Anzhen Hospital and 6 subcenters in China.

We planned to prospectively enroll 331 post–stent implantation patients with available CCTA data since June 2022, and invasive FFR will be performed within 3 months when clinically indicated. Patient recruitment is currently ongoing. Among them, 250 patients from Beijing Anzhen Hospital will be used to adapt and extend the existing DEEPVESSEL model, a deep learning–based CT-FFR computational software designed for the non-invasive functional assessment of coronary artery disease and previously validated in de novo coronary lesions, for application in the assessment of in-stent restenosis (ISR), and 81 patients from the other 6 subcenters will be used in external validation. Sensitivity, specificity, accuracy, positive predictive value, and negative predictive value with their corresponding 95% confidence intervals (CIs) were calculated for CT-FFR. The receiver operating characteristic (ROC) curve was analyzed, and the area under the curve (AUC) was calculated. The McNemar test and Bland-Altman plot will be used to examine the diagnostic consistency between CT-FFR and invasive FFR. The correlation was analyzed by Spearman’s correlation coefficient.

**Trial registration number:**

ChiCTR2200058822.

## Introduction

According to the 2026 Heart Disease and Stroke Statistics Update from the American Heart Association, the prevalence of coronary heart disease (CHD) among adults aged ≥20 years was 5.2% based on NHANES 2021–2023 data [1]. At present, Percutaneous coronary intervention(PCI) is still the main treatment strategy for CHD. With the increasing number of patients receiving stent implantation, the incidence of adverse events associated with stent implantation is increasing year by year. Even though drug-eluting stents (DESs) have dramatically reduced the rates of in-stent restenosis (ISR), the target lesion revascularization(TLR) caused by ISR still occurs at a rate of approximately 2% per year [2]. And compared with the PCI of de novo lesions, PCI caused by ISR is associated with a higher incidence of major adverse cardiovascular events(MACE) [3], which emphasizes the significance of early and accurate diagnosis in improving the prognosis of ISR patients.

The imaging diagnosis of ISR primarily relies on invasive coronary angiography (ICA) and coronary computed tomography angiography (CCTA). Currently, ICA remains the gold standard for ISR diagnosis, as it enables direct visualization of vascular morphology to obtain quantitative lesion parameters and allows assessment of ISR severity using the internationally standardized Mehran classification system [4]. Although CCTA demonstrates significant clinical value in evaluating acute chest pain owing to its noninvasive nature, its application in post-PCI patients remains constrained.

This stemmed primarily from imaging artifacts caused by stent material, geometric factors, and vessel wall calcification. Specifically, stent diameter, strut thickness, and associated blooming artifacts constitute major determinants of image quality degradation [5]. Additional confounding factors include patient heart rate and procedural complexity of the stent implantation, which may compromise the diagnostic accuracy of CCTA for ISR evaluation [6]. Consequently, current clinical guidelines do not recommend routine CCTA surveillance for post-PCI patients [7].

In 1993, [name] introduced the Fractional Flow Reserve (FFR). This hemodynamic index quantifies the functional significance of coronary artery stenosis by measuring the pressure ratio between the distal and proximal ends of a coronary artery stenosis [8]. Despite its diagnostic value, the widespread clinical adoption of FFR has been limited due to its invasive operation, procedural complexity, and the requirement for pharmacologically induced hyperemia.

In recent years, computed tomography-derived fractional flow reserve (CT-FFR), which combines computational fluid dynamics (CFD) with CCTA, has enabled noninvasive estimation of FFR by integrating coronary anatomical and functional data, thereby eliminating procedural risks and drug-induced adverse effects. Landmark prospective multicenter trials, including DISCOVER-FLOW [9], DeFACTO [10], and NXT [11], have consistently demonstrated the superior diagnostic performance of CT-FFR over purely anatomy-based CCTA, using invasive FFR as the reference standard. However, the computational complexity and prolonged processing time of conventional CT-FFR techniques hinder their utility in emergency settings and personalized medicine.

To overcome these limitations, researchers have proposed integrating artificial intelligence (AI) and deep learning with CT-FFR by developing deep learning algorithms trained on large-scale clinical datasets to establish fully automated CT-FFR computational models. Emerging evidence has demonstrated the clinical feasibility of this approach [12,13]. In a three-cohort randomized controlled trial, Guo et al. [13] reported that the deep learning-based automated CT-FFR system exhibited superior diagnostic performance, including higher accuracy, specificity, and area under the receiver operating characteristic curve (AUC) for detecting coronary stenosis. Notably, the system significantly reduced computational processing time and manual operator input(quantified by mouse clicks), demonstrating excellent user-friendliness.

Current research on CT-FFR has primarily focused on de novo coronary lesions, while its applicability to ISR requires further validation. In contrast to de novo lesions, which typically presents as uniform, concentric luminal narrowing due to neointimal hyperplasia, ISR has distinct diagnostic complexities. The metallic stent struts generate imaging artifacts on CCTA and alter local hemodynamics, compromising anatomical assessment accuracy. Moreover, ISR frequently manifests as diffuse lesions or multi-segment stent overlap, resulting in a poorer correlation between lumen stenosis severity and myocardial ischemia than de novo lesions [14]. Pinheiro et al. [15] conducted a comparative analysis of plaque characteristics between de novo coronary lesions and ISR lesions, demonstrating differences in neovascularization and macrophage infiltration that ultimately result in differential plaque stability and clinical outcomes.

Bozika et al. [16] systematically reviewed the clinical applications of CT-FFR, demonstrating its reliable diagnostic performance for ISR as well as its value in guiding clinical decision-making. In addition, CT-FFR enables physiology-based, precise virtual procedural planning by simulating post-intervention coronary physiology [17], thereby supporting more accurate identification of functionally relevant lesions, optimization of stent length and positioning, and reduction of potentially unnecessary revascularization, which is particularly important in patients with complex or multivessel coronary disease. Furthermore, the integration of CT-FFR with artificial intelligence has improved both diagnostic performance and computational efficiency, facilitating its implementation in routine clinical practice.

Through the development of a deep learning-based CT-FFR model incorporating optimized image reconstruction algorithms, we aim to minimize stent-induced artifacts affecting lumen boundary detection and computationally simulate the hemodynamic alterations caused by metallic stent struts, with the ultimate goal of achieving accurate diagnosis of ISR.

Therefore, we performed a multicenter, prospective diagnostic study with the following objectives: firstly, to develop a deep learning-based CT-FFR model for precise functional assessment of ISR, and secondly, to validate its diagnostic performance using invasive FFR as the reference standard.

## Method

### Study design

Adhering to the Standard Protocol Items: Recommendations for Interventional Trials (SPIRIT) 2013 Statement, we have outlined the trial design and protocol in detail (Fig 1).

**Fig 1 pone.0346723.g001:**
[figure not shown]
Schedule of the trial.

This study will be carried out in Beijing Anzhen Hospital and 6 subcenters (Fuwai Hospital, Chinese Academy of Medical Sciences, Beijing Tongren Hospital, Beijing Hospital, Beijing Chaoyang Hospital, Xuanwu Hospital) in China. From June 2022, consecutive post-stent patients with available CCTA data were prospectively enrolled. Invasive FFR will be performed according to clinical and imaging indications within 3 months of CCTA. For the purposes of supplementary training and diagnostic performance analysis, only patients with available invasive FFR measurements will be included. Patients without invasive FFR data will be excluded. Among them, 250 patients from Beijing Anzhen Hospital will be used to adapt and extend the existing DEEPVESSEL model [18], a deep learning–based CT-FFR computational software designed for the non-invasive functional assessment of coronary artery disease and previously validated in de novo coronary lesions, for application in the assessment of in-stent restenosis (ISR), and 81 patients from the other 6 subcenters will be used in external validation (Fig 2).

**Fig 2 pone.0346723.g002:**
[figure not shown]
Study diagram.

The main inclusion criteria were post-stent patients with available CCTA data, and invasive FFR was performed within 3 months according to clinical and imaging indications. The main exclusion criteria are: (1)recent(＜3 months) acute coronary syndrome, (2)coronary artery bypass grafting(CABG) history, (3)severe calcification(Agatston≥400), (4) left ventricular ejection fraction(LVEF)≤40%, (5)significant valvulopathy, (6)cardiac arrhythmias requiring therapeutic intervention, or (7)cardiac metallic devices(e.g., prosthetic valves, cardiovascular implantable electronic devices). (Table 1)

**Table 1 pone.0346723.t001:** Inclusion and exclusion criteria.

Inclusion criteria	Exclusion criteria
(1) post-stent patients with available CCTA data	(1) recent (<3 months) acute coronary syndrome
(2) invasive FFR was performed within 3 months according to clinical and imaging indications	(2) coronary artery bypass grafting (CABG) history
	(3) severe calcification(Agatston≥400)
	(4) left ventricular ejection fraction(LVEF)≤40%
	(5) significant valvulopathy
	(6) cardiac arrhythmias requiring therapeutic intervention
	(7) cardiac metallic devices (e.g., prosthetic valves, cardiovascular implantable electronic devices)

This study is a prospective study, and informed consent has been obtained. This trial does not involve collecting biological samples for storage.

### Study process

Prospective patients enrollment for this study began in June 2022 and is currently ongoing. Data collection (including demographic information, imaging data, laboratory tests, and interventional procedure parameters) and data analysis are scheduled to be finalized in 2026.

During the data collection process, all information will undergo rigorous de-identification to ensure that researchers will not have access to any personally identifiable information of participants at any stage.

Patients will be prospectively enrolled into the study, and their CCTA and invasive FFR data will be systematically collected according to this protocol. All data, including demographic characteristics, medical history, laboratory results, and clinical examinations (ECG, ICA, CCTA, and echocardiography), will be systematically recorded and stored using an electronic data capture (EDC) system.

All CCTA examinations will be acquired using multidetector CT scanners with ≥64 detector rows, in strict adherence to the 2022 Society of Cardiovascular Computed Tomography(SCCT) guidelines. When the CCTA image quality is suboptimal (e.g., obvious motion artifacts or blooming artifacts) or couldn’t satisfy the subsequent CT-FFR analysis, the patient will be censored out. Because this study is still ongoing and patient enrollment has not yet been completed, patients excluded due to poor image quality will be replaced by continued recruitment until the predefined sample size is reached.

FFR will be performed in intermediate stenosis (30–90% stenosis in vessel diameter) with a vessel size of at least 2 mm based on clinical symptoms suggestive of myocardial ischemia according to standard practice by experienced invasive cardiologists. Pressure calibration should be confirmed as zero at the proximal segment of the coronary arteries. After calibration, the pressure wire should be advanced to the distal end of the stenosis. Maximal myocardial hyperaemia should be induced by continuous intravenous adenosine infusion via a central or peripheral vein with an infusion rate of 140 μg/kg/min. At the same time, the distal coronary artery pressure at the pressure sensor and the proximal pressure at the coronary ostium will be recorded. A pullback recording should be performed and recorded. The absence of pressure signal drift needs to be confirmed at the distal end of the guiding catheter.

To ensure consistency across centers, the same criteria for FFR indication and standardized procedural protocols had been applied at Beijing Anzhen Hospital and all participating subcenters. All investigators underwent consistent training before study initiation.

CCTA and invasive FFR data of 250 prospectively enrolled patients at Beijing Anzhen Hospital will be transmitted to Keya Medical for supplementary training of the existing DEEPVESSEL FFR model. Following model establishment, the algorithm will be applied to analyze CCTA images from 81 prospectively enrolled patients in the 6 subcenters to derive CT-FFR values for external validation. Diagnostic performance for ISR detection will be rigorously evaluated using invasive FFR as the reference standard (threshold ≤0.80).

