### Sample size calculation

The sample size calculation was based on previous studies [19] and the following hypothesis: At the patient level, CT-FFR demonstrated an AUC of 0.73(95% CI: 0.55–0.87) for detecting ISR, with a disease prevalence of 76%. A sample size calculation was performed using PASS 2021 (Test for One ROC Curve) with α = 0.05, power = 0.9, and two-tailed testing, yielding a required sample size of 77 patients. We planned to prospectively enroll 81 patients in the external validation cohort, which was expected to provide 90% power to detect an AUC of 0.73.

The training cohort size was defined based on data availability and a predefined training-to-validation ratio of approximately 3:1 to balance model development and independent performance evaluation. Therefore, at least 243 patients were required for model training. Considering clinical practice and data availability, we prospectively planned to enroll 250 patients to meet the sample size requirement, which is comparable to or even larger than the training cohort sizes reported in previous study [20].

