## Discussion

This study is a multicenter, prospective, diagnostic study, aiming to establish a deep learning-based CT-FFR model for the accurate assessment of ISR and to validate its diagnostic performance using invasive FFR as the reference standard. The expected outcome is a strong correlation and good diagnostic consistency between the CT-FFR model and invasive FFR. Through the development of this model, the anatomical and functional assessments of ISR lesions are effectively integrated, reducing the impact of stent structure and other factors on CCTA image quality. This model enables precise diagnostic results without invasive procedures, significantly optimizing the diagnostic process and improving treatment efficiency.

Previous studies on CT-FFR have primarily focused on de novo coronary lesions, with limited research on the CT-FFR model for ISR lesions. Therefore, this study specifically constructs a CT-FFR model for ISR lesions. Compared to other studies, this study was based on a fully automated CCTA image processing and deep learning–based analytical framework using a Deep Bidirectional Long-term Recurrent Neural Network (DBL-RNN) for CT-FFR estimation. The framework performs automated three-dimensional reconstruction of the coronary arteries and centerline-level feature extraction. Local vascular morphology, stenosis-related characteristics, and upstream and downstream global information are integrated within a bidirectional recurrent neural network, which captures relationships along the vessel path and the overall structure of the coronary artery tree. As a result, continuous CT-FFR values can be estimated along the entire coronary artery. During model training, dropout regularization and Adam optimizer were applied to improve model stability and generalizability, providing a novel approach for non-invasive functional assessment of coronary lesions.

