## Limitation

First, patients with coronary artery bypass grafting (CABG), acute coronary syndrome (ACS), and other specific conditions were excluded. In addition, although this was a multicenter study, both the supplementary training and external validation cohorts were derived from Beijing Anzhen Hospital and six other hospitals located in Beijing. Therefore, the applicability of the model and long-term prognostic value for post-stent implantation patients requires further investigation.

Second, an internal validation of coronary artery segmentation accuracy was not planned in this study. Although the segmentation component is based on an established and previously validated CCTA processing framework, segmentation accuracy was not evaluated as a primary endpoint in the present study, which focused primarily on the diagnostic performance of CT-FFR. Consequently, residual segmentation errors may have influenced CT-FFR estimation in certain cases. Future studies incorporating systematic assessment of segmentation accuracy and its impact on CT-FFR performance may further enhance model interpretability and robustness.

In addition, exclusion of patients with suboptimal CCTA image quality may introduce selection bias. Patients with severe coronary calcification or substantial imaging artifacts may be excluded from the final analysis cohort. Consequently, the diagnostic performance of the trained model may be overestimated and may not fully reflect its performance in real-world populations with suboptimal imaging conditions.

Finally, invasive FFR is performed according to clinical and imaging indications rather than as part of a study-mandated protocol uniformly applied to all patients. Consequently, referral and verification bias may be present. If a relatively high prevalence of functionally significant ISR is observed in final results, this would suggest that the cohort represents a clinically selected population rather than a real-world post-stent population. As a result, the reported diagnostic performance, including sensitivity, specificity, and AUC, may not fully reflect performance in broader post-stent populations. Further validation in less selected populations will be warranted.

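### Unusable scans are removed and replaced in the validation cohort, so reported accuracy covers evaluable scans only and cannot by itself show that stent artifact has been overcome

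*Protocol article*

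**What the plan says.** The trigger for removal, in the Study process section, opens "When the CCTA image quality is suboptimal (e.g., obvious motion artifacts or blooming artifacts" and goes on to add scans that cannot support the later CT-FFR analysis. The consequence is that "the patient will be censored out", and then "patients excluded due to poor image quality will be replaced by continued recruitment until the predefined sample size is reached". Nothing limits the rule to the training cohort, so it also applies to the 81 external-validation patients.

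The Statistics section calculates sensitivity, specificity, predictive values, accuracy and AUC from CT-FFR against invasive FFR. It has no category for a scan that yields no usable CT-FFR value.

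On purpose, the Introduction says "we aim to minimize stent-induced artifacts affecting lumen boundary detection". The Discussion lists among the model's benefits "reducing the impact of stent structure and other factors on CCTA image quality".

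The Limitation section acknowledges that "exclusion of patients with suboptimal CCTA image quality may introduce selection bias" and that "the diagnostic performance of the trained model may be overestimated".

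**The concern.** The Introduction names stent material, strut thickness and blooming as the main reasons why CCTA performs poorly after stenting, and the model is meant to deal with them. A validation set from which scans with obvious blooming have been taken out cannot test that aim at the point where it is hardest. The metrics answer a narrower question: how well does CT-FFR agree with FFR when the scan is good enough?

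The trigger is also wider than technical failure. A scan may be dropped for being suboptimal even if the software could have produced a value from it. Because replacement tops the cohort up to its target, a final count of 81 is the same whatever the failure rate, and so carries no information about it. A reader who takes the accuracy table as performance in stented patients sent for FFR would be too optimistic by an unknown amount.

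**Working it through.** **1. The plan's own figure.** The Sample size calculation section gives AUC 0.73, prevalence 76%, α = 0.05 and "power = 0.9, and two-tailed testing, yielding a required sample size of 77 patients". The null AUC is not stated; 0.5 is assumed here. With the Hanley–McNeil variance,

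power = Φ((|A₁ − A₀| − 1.96·√V₀) / √V₁).

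At N = 78 (59 diseased, 19 not), √V₀ = 0.0766 and √V₁ = 0.0607, so power = Φ((0.23 − 1.96 × 0.0766)/0.0607) = Φ(1.32) ≈ 0.91. The smallest N reaching 90% is 78, against 77 stated. Power is 0.893 at 77 and 0.91 at 81. The sample size is not in dispute; it counts evaluable scans.

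**2. Patients behind 81 evaluable scans.** With failure share f (assumed, as the document gives none), the number of otherwise eligible patients needed is 81/(1 − f), rounded up: 86, 90, 102 and 108 at f = 5, 10, 20 and 25%. That leaves 5, 9, 21 and 27 outside the denominator.

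**3. Effect on accuracy.** Assumed: evaluable-only sensitivity 0.85, specificity 0.80, and failure unrelated to FFR status. From the protocol: prevalence 0.76. Evaluable-only accuracy = 0.76 × 0.85 + 0.24 × 0.80 = 0.838.

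- Failures counted as positive: sensitivity = 0.85(1 − f) + f; specificity = 0.80(1 − f).
- Failures counted as misclassified: sensitivity, specificity and accuracy are each multiplied by (1 − f).

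| f | Positive: sens. | Positive: spec. | Positive: acc. | Misclassified: sens. | Misclassified: spec. | Misclassified: acc. |
|---|---|---|---|---|---|---|
| 5% | 0.858 | 0.76 | 0.834 | 0.81 | 0.76 | 0.80 |
| 10% | 0.865 | 0.72 | 0.830 | 0.77 | 0.72 | 0.75 |
| 20% | 0.880 | 0.64 | 0.822 | 0.68 | 0.64 | 0.67 |
| 25% | 0.888 | 0.60 | 0.819 | 0.64 | 0.60 | 0.63 |

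Check at 25%, failures positive: 0.76 × 0.8875 + 0.24 × 0.60 = 0.6745 + 0.144 = 0.8185.

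**4. Why specificity is the sensitive quantity.** At 76% prevalence, 81 patients contain about 19 who are FFR-negative (0.24 × 81 = 19.4). One further FFR-negative patient with an unusable scan, counted as positive, takes specificity from 0.80 to 0.80 × 19/20 = 0.76.

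**5. AUC.** If failed scans carry no information and are equally common in both groups, AUC over all patients = 0.73(1 − f)² + 0.5[1 − (1 − f)²], which is 0.708, 0.686 and 0.647 at 5, 10 and 20%.

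**The case against.** The case for leaving the plan alone has four parts, and much of it stands.

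- **The bias is disclosed, with its direction.** The Limitation section says performance may be overestimated and may not carry over to suboptimal imaging. That deserves credit. It does not give a reader any means of judging how large the overestimate is.
- **Blinding is already in place for the computation.** In the validation phase, those who compute CT-FFR see only anonymised CCTA images and are blinded to FFR, angiography reports and clinical diagnoses. A reader might infer that quality exclusions are made knowing the FFR result; the document does not say so, and a failure found during computation would be found blind. What remains open is who makes the image-quality decision and when.
- **FFR may not exist for every removed patient.** A reader might infer from Table 1, where FFR has already been performed, that each dropped patient has a reference result. The Study design section, however, describes enrolment on available CCTA with FFR to follow when indicated, and the Study process section sets out the quality rule before the FFR step. The order is ambiguous, so some removed patients may be unverified and could not enter an accuracy table.
- **An exclusion count may appear elsewhere.** Data go into an electronic capture system, the study diagram is not shown, and a condensed article leaves reporting detail to other documents. It cannot be said that the loss will go unreported. The removal-and-replacement rule itself, however, is fixed in the text.

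Two further limits apply. Motion artifact is not specific to stents, so the conflict with the stated aim rests on blooming and on stented segments that cannot be processed. And the examples given are obvious artifacts, so scans with lesser strut artifact can remain.

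**Conclusion.** The point holds in a limited form and should be fixed. The external-validation metrics are conditional on an evaluable scan, and by themselves they cannot support a claim that stent artifact has been overcome. The protocol names the likely overestimation but plans nothing to measure it.

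The true size cannot be found from the document. The illustration rests on assumed sensitivity, specificity and failure shares of 5–25%, with failure independent of disease. If failure rates differ between FFR-positive and FFR-negative patients, each group's own rate replaces f in the formulas.

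A reader might infer that both sensitivity and specificity fall once failures are counted. Under the failures-as-positive rule only specificity falls; sensitivity rises, and accuracy barely moves (0.838 to 0.834–0.819) because prevalence is high. Sensitivity falls only under the worst-case rule, where accuracy drops to about 0.80–0.63. Nor does the point show any error in the sample size.

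**What to change.** For the validation cohort only:

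1. Make and lock the image-quality decision on the CCTA alone, blind to FFR, extending to this decision the blinding already given to CT-FFR computation.
2. Report the number and share of otherwise eligible patients excluded for image quality, split by whether invasive FFR is available.
3. Beside the evaluable-only results, report an intention-to-diagnose table for all FFR-verified patients with non-evaluable scans counted as CT-FFR positive, and a worst-case table with them counted as misclassified.

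Recruitment to 81 evaluable patients can continue, so the planned precision for the AUC is kept, and exclusion from training can stay. Enrolment is ongoing, so this can be specified before analysis. The cost is some plan wording, a log of image-quality exclusions and the added tabulation. The downside for the study is a less favourable specificity, with sensitivity also lower in the worst case.

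### The performance figures are named for detection of in-stent restenosis, but the reference FFR spans everything from ostium to sensor, so positives due to native disease can be credited to the stent

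*Protocol article*

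**What the plan says.** **Target.** Study process, on the validation cohort: "Diagnostic performance for ISR detection will be rigorously evaluated using invasive FFR as the reference standard (threshold ≤0.80"). Sample size calculation likewise presents its AUC of 0.73 and prevalence of 76% as figures for detecting ISR.

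**Measurement.** Study process: "After calibration, the pressure wire should be advanced to the distal end of the stenosis", after which "the distal coronary artery pressure at the pressure sensor and the proximal pressure at the coronary ostium will be recorded". The Introduction describes FFR differently, as "measuring the pressure ratio between the distal and proximal ends of a coronary artery stenosis". A further instruction in Study process is "A pullback recording should be performed and recorded".

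**Who is measured.** The indication is "FFR will be performed in intermediate stenosis (30–90% stenosis in vessel diameter) with a vessel size of at least 2 mm", with symptoms suggesting ischaemia. The main criteria begin: "The main inclusion criteria were post-stent patients with available CCTA data"; they add an FFR within 3 months. None of the listed exclusions concerns native disease in the stented vessel.

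**Analysis.** CT-FFR calculation takes the CT-FFR value at the position of the pressure-wire sensor. Statistics restricts the diagnostic analysis to stented segments with an FFR measurement and applies 0.80 to both tests to define a functionally significant lesion. At patient level, the stented vessel with the lowest FFR represents the patient.

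**The concern.** The target condition named in the plan is narrower than what the reference standard measures. An ostium-to-sensor ratio does not show how much of the pressure loss occurs inside the stent. If a stented vessel has a native lesion upstream of the sensor, or if the stenosis that prompted FFR lies outside the stent, FFR can be 0.80 or lower with little or no contribution from restenosis. CT-FFR at the same point would also tend to be low, and the match would count as a correct detection of ISR.

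This bears on the trial's own question. The Introduction argues that stents create particular difficulties for CT-based assessment, and Study design says the existing software was already validated in de novo lesions. Correct calls driven by native disease could therefore hide weaker performance inside the stent. The pullback trace could help separate the two, but no use of it is stated.

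**Working it through.** **1. What the ratio covers.** Its two pressures are taken at the ostium and at the sensor, and the sensor sits at the distal end of the stenosis. Lesions between those points count; lesions beyond the sensor do not. Illustration, adding drops as an approximation: a native drop of 0.10 and an in-stent drop of 0.11 give 1 - 0.10 - 0.11 = 0.79, which is positive. The in-stent drop alone gives 1 - 0.11 = 0.89, which is negative.

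**2. The plan's own figures.** The sample size of 77 can be approximated. A two-sided one-sample AUC test at α = 0.05 and 90% power, with AUC 0.73, 76% positive, an assumed null AUC of 0.50 and Hanley-McNeil variance, gives 78. The present point does not alter that number. For the expected split, 81 × 0.76 = 61.6, so about 62 FFR-positive and 19 FFR-negative patients.

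**3. Share of positives due only to another lesion.** The documents give no frequency of additional lesions, so every input here is an assumption:
- In-stent drop: absolute value of a normal variable with SD 0.10.
- Other lesion: present in 20%, 30% or 40% of vessels, with drop the absolute value of a normal variable with mean 0.08 and SD 0.04.
- Drops add, and every other lesion lies upstream of the sensor.
- Positive means total drop ≥0.20. Positive only because of the other lesion means positive with in-stent drop <0.20.

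| Mean in-stent drop | Other lesion present | Vessels positive | Share of positives due only to the other lesion |
|---|---|---|---|
| 0.15 | 20 / 30 / 40% | 37 / 40 / 43% | 17 / 23 / 29% |
| 0.25 | 20 / 30 / 40% | 73 / 75 / 77% | 5 / 8 / 10% |

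The first row implies far fewer positives than the 76% on which the trial is planned. The second row is close to that prevalence, so about 5-10% is the share to use. The planned 76% is a patient-level figure and is applied to vessels here as an approximation. If half of the other lesions lay beyond the sensor (a further assumption), the second row would fall to about 3 / 4 / 5%.

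**4. Consequence for specificity.** Suppose CT-FFR classifies exactly as FFR does. Reported sensitivity and specificity are then both 100%. Patients positive only because of native disease are false positives for ISR:

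specificity for ISR = 19 / (19 + k), PPV for ISR = (62 - k) / 62

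- Share about 5%, k = 3: specificity 19/22 = 86%, PPV 59/62 = 95%.
- Share about 10%, k = 6: specificity 19/25 = 76%, PPV 56/62 = 90%.

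With only about 19 negatives, a few misattributed positives move specificity a long way.

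**The case against.** The strongest reply is that index and reference tests are equally cumulative. CT-FFR is taken at the sensor position and cut at the same 0.80, so agreement between them is not biased by lesions elsewhere. That stands. A reader might infer that the planned accuracy figures are inflated, but as measures of CT-FFR against FFR they are not. Inflation of in-stent performance needs the further assumption that the model does better on native than on stented segments, which is plausible but not shown.

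The plan also already uses functional language: Statistics refers to functionally significant lesions and limits the analysis to measured stented segments. This narrows the point without removing it, because no stated rule assigns the pressure drop to the stent, and Study process and Sample size calculation still name ISR as what is detected.

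Three stronger readings are not supported:
- That FFR adds up all disease in the vessel. It covers only what lies between ostium and sensor.
- That native lesions are routinely labelled as restenosis. They can be; how often is not given.
- That the pullback will never be used. This is a condensed article, and a fuller plan may give it a role; one can say only that none is stated here.

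Finally, in-stent analyses will be imprecise in a cohort with about 19 negatives. That is correct, and it is why they belong among the secondary analyses.

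**Conclusion.** The concern holds as a mismatch between the named target and the reference standard. Followed as written, the plan estimates how well CT-FFR identifies functionally significant stenosis upstream of the sensor in a stented vessel, and reports this as detection of ISR. The Limitation section discusses referral, verification and image-quality selection, but not serial or native lesions.

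The size depends on inputs that the documents do not give. Under the assumptions above, with positivity near the planned 76%, about 5-10% of positives would owe their status to another lesion, and fewer if some lesions lie beyond the sensor. For a CT-FFR in perfect agreement with FFR, that would mean a specificity for ISR of about 86% to 76% against a reported 100%. Shares of 17-29% arise only if about 37-43% of vessels are positive, which does not fit the planning prevalence. The sample size is unaffected. The change is worth making because it is cheap and enrolment is still open.

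**What to change.** 1. State the primary target as functionally significant stenosis in a stented vessel. Reconcile the description of FFR in the Introduction, the measurement and the ISR wording in Study process, the analysis unit in Statistics and the wording in Sample size calculation.
2. Prespecify two secondary analyses, each with confidence intervals:
   - Sensitivity, specificity and AUC in vessels where the stented segment is the only stenosis of at least 30% upstream of the sensor.
   - A Bland-Altman comparison of the trans-stent pressure drop from the recorded pullback with the CT-FFR drop across the same segment. No AUC should be attached to it, because no cut-off for that drop is defined and drops across serial lesions interact.
3. Limit claims about performance inside the stent to these two results, and mention serial and native lesions under Limitation.

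The cost is rewording and some extra reading of recordings that the protocol already requires; no new procedure or patient is needed. The restricted subset will be small and its specificity imprecise.
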